## Abstract

**Background:**

Hiking is one of the most popular forms of exercise in the alpine region. However, besides its health benefits, hiking is the alpine activity with the highest incidence of cardiac events. Most incidents occur due to overexertion or underestimation of the physiological strain of hiking.

**Objective:**

This project will establish a standardized cardio trekking test trail to evaluate the exercise capacity of tourists within hiking areas and deliver a tool for the prevention of hiking-associated cardiac incidents. Further, individual exercise intensity for a hiking tour will be predicted and visualized in digital maps.

**Methods:**

This cooperation study between Austria and Germany will first validate a 1-km outdoor cardio trekking test trail at 2 different study sites. Then, exercise intensity measures on 8-km hiking trails will be evaluated during hiking to estimate overall hiking intensity. A total of 144 healthy adults (aged >45 years) will perform a treadmill test in the laboratory and a 1-km hiking test outdoors. They will wear a portable spirometry device that measures gas exchange, as well as heart rate, walking speed, ventilation, GPS location, and altitude throughout the tests. Estimation models for exercise capacity based on measured parameters will be calculated.

**Results:**

The project “Connect2Move” was funded in December 2019 by the European Regional Development Fund (INTERREG V-A Programme Austria-Bavaria – 2014-2020; Project Number AB296). “Connect2Move” started in January 2020 and runs until the end of June 2022. By the end of April 2022, 162 participants were tested in the laboratory, and of these, 144 were tested outdoors. The data analysis will be completed by the end of June 2022, and results are expected to be published by the end of 2022.

**Conclusions:**

Individual prediction of exercise capacity in healthy individuals with interest in hiking aims at the prevention of hiking-associated cardiovascular events caused by overexertion. Integration of a mathematical equation into existing hiking apps will allow individual hiking route recommendations derived from individual performance on a standardized cardio trekking test trail.

**Trial Registration:**

ClinicalTrails.gov NCT05226806; https://clinicaltrials.gov/ct2/show/NCT05226806

**International Registered Report Identifier (IRRID):**

DERR1-10.2196/39038

## Introduction

Regular physical activity improves exercise capacity [1,2] and reduces the risk of developing cardiovascular diseases [3]. Endurance and strength training have the highest levels of evidence in current national and international guidelines as therapeutic components for the prevention and rehabilitation of cardiovascular diseases [4]. Hiking is a popular mode of exercise in mountainous regions worldwide and is being performed by millions of people, including those with an increased cardiovascular risk [5]. Despite its well-known beneficial effects on the cardiovascular system, intensive and exhaustive physical activities can lead to cardiac events, especially in untrained individuals. As a result, hiking is the alpine activity with the highest incidence of cardiac events, including sudden cardiac death [6-8]. These critical incidents occur mostly due to overestimating personal fitness and choosing overly demanding hiking routes or neglecting weather conditions (temperature, wind, rainfall, snow, etc). In few cases, hikers know about their higher risk and prevent incidents during hikes through medical prevention check-ups beforehand. Such a check-up for heart health and an evaluation of the exercise capacity during standard conditions could ideally be done by a simple ergometry test. Based on its results, training and hiking recommendations could be given by an expert. To further enhance the safety of hiking as a means of preventing cardiovascular disease and helping prevent cardiac incidents, this study aims to develop and validate a standardized 1-km cardio trekking test trail (CTTT) that can be set up in mountainous areas to determine individual physical fitness levels and personalize categories of exercise intensities during walking and hiking. Additionally, we will perform scientific mapping of 2 cardio trekking trails based on several performance parameters, such as heart rate and gas exchange. The realization of those study aims should not substitute the medical prevention examination but rather provide an additional prevention method to predict cardiovascular demand in individual hikers.

This study is part of a larger project that aims to appreciate natural and evidence-based cardio trekking trails through open innovation methods for the sustainable promotion of cross-generational health-oriented tourism, called “Connect2Move.” The project has been funded by the European Regional Development Fund (INTERREG V-A Programme Austria-Bavaria – 2014-2020; Project Number AB296). This project aims to redesign existing hiking routes into themed trails and digitally redesign those trails. Expected cardiovascular load based on individual cardiorespiratory fitness will be visualized in digital maps, in addition to the usual description of the length, altitude, path condition, and duration. For valorization and implementation in the participating communities, an open innovation approach is chosen, which involves regional stakeholders and the target population early in the development process, and is scientifically and medically supervised. Two cross-border, climate-friendly, biological concepts for physical activity promotion/cardio trekking in the Alps will be developed. The ideas can increase year-round gentle health tourism and promote individual health literacy for tourists and locals.

## Methods

### Study Design

This cross-sectional study to reduce the risk of cardiac events in hiking consists of 3 work packages. It will be conducted in Salzburg and Werfenweng, Austria, as well as in Prien am Chiemsee and Aschau im Chiemgau, Germany. The first work package establishes and validates a 1-km CTTT. The second work package analyzes the physiological aspects of an 8-km trekking trail (Figure 1). In the third work package, developing an algorithm to calculate exercise intensity based on the results of the CTTT is the main task. This work package includes the cartography of intensities over the 8-km trekking trail. The first and second work packages will be performed by the Ludwig Boltzmann Institute for Digital Health and Prevention Salzburg and the Technical University Munich, and the third work package will be performed by Salzburg Research. The laboratory testing and medical assessment of the Austrian participants will be performed at the University Institute of Sports Medicine, Prevention and Rehabilitation, Paracelsus Medical University Salzburg, Austria, and the testing and assessment of the German participants will be performed at St. Irmingard Klinik in Prien am Chiemsee, Germany.

**Figure 1 figure1:**
[figure not shown]
From laboratory testing to tourist hikes. (A) Laboratory treadmill test. Evaluation of maximal exercise capacity and training zones. (B) 1-km cardio trekking test trail. Evaluation of exercise capacity in a standardized outdoor setting. (C) 8-km cardio trekking trail. Guided hikes with study participants, with measurement of exercise capacity and heart rate during the hike. (D) Cartography of the 8-km cardio trekking trail with the help of guided tourist hikes. bpm: beats per minute; HR: heart rate; HR_avg_: average heart rate; HR_max_: maximal heart rate; VO_2_: oxygen uptake; VO_2max_: maximal oxygen uptake.

### Ethics Approval

Inclusion and exclusion criteria are described in Textbox 1. Participants will have to provide written informed consent before participating in the study. The Ethics Committee of the State of Salzburg (EK-Nr.: 1090/2020) and the Ethics Committee of the Medical Faculty of the Technical University of Munich (527/20S) have approved this study. Further, the study has been registered at ClinicalTrials.gov (NCT05226806). The study will be conducted following the ethical guidelines of the Declaration of Helsinki.

Inclusion and exclusion criteria.
**Inclusion criteria**
Age >45 yearsAny sexSigned informed consentNo relevant pathologies found during initial laboratory testing
**Exclusion criteria**
Acute or chronic cardiovascular diseases, including untreated or insufficiently treated arterial hypertension (systolic blood pressure ≥140 mmHg or diastolic blood pressure ≥90 mmHg)Acute or chronic lung diseasesLiver diseasesKidney diseasesDiabetes mellitusAlcohol (>30 g/day) or drug abuseBMI >35Orthopedic restriction precluding physical activities performed during the studyPregnancy

### Recruitment Process and Measurement Process

The recruitment of participants will be conducted using the different information channels of the included institutes via the project website, recruitment flyers, and word-of-mouth advertising. If potential participants are >45 years of age, they will be informed about the study objectives, evaluation protocol, and procedures. On agreeing to participate, they will be invited to the initial laboratory testing at 1 of the 2 testing sites. At the beginning of the initial testing, researchers will provide detailed information about the study again, and the participants will be asked to read and sign written informed consent.

Participants will have to perform 3 different exercise testing procedures to complete the study, including 1 laboratory test on a treadmill and 2 field tests (1-km CTTT and 8-km hikes) in Werfenweng, Austria, or Aschau im Chiemgau, Germany. There will be at least 1 full day of rest between the laboratory test and the first field test. The 1-km CTTT and 8-km hikes will be performed on 2 days. If the scheduling of 2 days is not possible, the 1-km CTTT and 8-km hikes will be conducted on the same day with at least 1 hour of rest in between. Half of the study population will participate in Austria, and the other half will participate in Germany.

### Laboratory Testing

The baseline testing will start with a detailed examination by a specialist in internal medicine. Measurements will include anthropometrics (weight, height, and BMI), pulmonary function testing (spirometry), resting electrocardiography (ECG), blood pressure, patient history, echocardiography, and blood testing (lipids, electrolytes, markers of kidney and liver function, thyroid hormones, glucose, and blood count), as well as risk scores for cardiac events in the next 10 years, including the prospective cardiovascular Münster study (PROCAM) Score [9], Framingham Score [10], and European Society of Cardiology (ESC) Score [11]. Other health information will be collected via a face-to-face interview by trained staff. It will include personal questions regarding smoking and alcohol consumption, and sociodemographic data (education, employment status, and marital status). Participants will be asked to fill out standardized questionnaires on physical activity (International Physical Activity Questionnaire [IPAQ] short form [12]) and health (Health Survey Questionnaire: 36-Item Short Form Health Survey [SF-36] [13]). Before exercise capacity is measured, it will be estimated based on a resting test protocol called the Polar Fitness Test, using the Polar beat app and a chest-strap ECG-based heart rate monitor (Polar Electro). The last part of the baseline testing will be an all-out spiroergometry test on a treadmill. The participants will wear the portable spirometry device K5 (Cosmed) to measure respiratory gas exchange throughout the test. The gas analysis will occur in the K5’s dynamic mixing chamber (DMC) mode. Heart rate will be measured using a Garmin chest strap. In addition, the participants will wear a 12-lead ECG device (Amedtec Medizintechnik Aue GmbH) for evaluation of exercise-dependent ECG changes, as well as a Garmin Vivoactive 4 smartwatch, which will measure wrist-based heart rate values from an optical sensor throughout the treadmill test. All 3 measurement methods for heart rate will be started simultaneously. The modified Bruce protocol [14] will be used as the treadmill test protocol and will start with 3 min at 2.4 km/h and 0% incline, followed by 3 min at 2.4 km/h and 5% incline. After the first 2 stages, the traditional Bruce protocol will be followed. The test will be stopped if participants reach maximal exhaustion or start running. At the end of each stage, the participants will be asked to indicate their rate of perceived exertion (RPE) on a printed 6-20 Borg scale [15], including a maximum value at test termination. Based on the spiroergometry results measured via the K5 device, ventilatory thresholds for each participant will be determined by the V-slope method [16]. Exercise recommendations (heart rate zones) for the 8-km hike will be made based on these thresholds.

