### Primary and Secondary Outcomes

#### Primary Outcome

The primary outcome is estimating the exercise capacity based on physiological features, subjective performance parameters, and route characteristics collected for 2 cardio trekking test routes in Werfenweng, Austria, and Aschau im Chiemgau, Germany. The 2 test routes have a length of approximately 1 km and a gradient of up to 26%. Participants will hike 1 of the 2 test routes shortly after the laboratory measurement. Based on these data and in combination with the capacity of maximal oxygen uptake (VO_2max_) derived in the laboratory setting, a statistical model for the prediction of VO_2max_ will be developed.

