#### Comparison of Resting Evaluation Versus Exercise Test for Exercise Capacity

We will measure the maximal exercise capacity (VO_2max_) during the use of the modified Bruce protocol on the treadmill. As we will use the portable spirometry device K5 from Cosmed, we will be able to use the DMC method instead of the breath-by-breath measurement.

As we will obtain measured VO_2max_ values, we will be able to compare those results with estimations for this parameter, which we will obtain with the Polar Fitness Test. This test is a 5-min resting evaluation performed with a chest strap and the Polar beat app. Based on the measured heart rate variability and added data like age, gender, weight, height, and fitness classification, the app will estimate the individual’s VO_2max_.

In addition, we will obtain VO_2max_ estimation based on the outdoor hikes that involve recording with the Garmin Vivoactive 4 smartwatch.

We aim to evaluate the validity of the 2 VO_2max_ estimations.

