#### Estimation Model for Exercise Capacity

As the first step in model development, the data collected in the laboratory and the results from the 1-km CTTT and 8-km hike will be analyzed descriptively to identify anomalies in the data, such as outliers or data loss due to possible device crashes. Based on these analyses, the data for Austria and Germany will be cleaned.

Following the principle “from the lab to the field,” the first estimation model will be developed based on features collected in the laboratory to verify how accurate and reliable VO_2max_ can be estimated. When the proof of concept works on the laboratory data, an in-field estimation model will be created based on the CTTT measurements to see if VO_2max_ from the laboratory can be determined based on the data collected on the CTTT. The derived estimation models will be validated with cross-validation and evaluation metrics (eg, adjusted R-squared and mean absolute error).

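### The treadmill test also ends when a participant starts to run, yet every peak is used as measured VO2max, which can flatten the primary prediction model by an unknown amount

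*Protocol article*

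**What the plan says.** All statements are in the protocol article.

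- Laboratory Testing, nature of the test: "The last part of the baseline testing will be an all-out spiroergometry test on a treadmill".
- Laboratory Testing, how it ends: "The test will be stopped if participants reach maximal exhaustion or start running".
- Laboratory Testing, stages: "After the first 2 stages, the traditional Bruce protocol will be followed". The speeds and inclines of those later stages are not given.
- Laboratory Testing, perceived exertion is collected on the Borg scale, "including a maximum value at test termination". Gas exchange and heart rate are recorded throughout.
- Comparison of Resting Evaluation Versus Exercise Test for Exercise Capacity, on how the result is labelled: "We will measure the maximal exercise capacity (VO_2max_) during the use of the modified Bruce protocol on the treadmill". The same section uses this value to judge the Polar and Garmin estimates.
- Primary Outcome: from the trail data and the laboratory value, "a statistical model for the prediction of VO_2max_ will be developed".
- Estimation Model for Exercise Capacity: the trail model is built "to see if VO_2max_ from the laboratory can be determined based on the data collected on the CTTT". Validation is by cross-validation, with adjusted R-squared and mean absolute error as examples of metrics.

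**The concern.** The two stopping reasons do not measure the same thing. Exhaustion is a limit of effort; starting to run is a change of gait. Someone who breaks into a run with effort in reserve leaves a peak below the true maximum. That value is right-censored: the true VO2max is at least as high.

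This falls unevenly. Less fit participants tend to reach exhaustion while still walking, so the cut-off applies mainly to the fitter. Participants are healthy adults over 45, and the listed criteria set no upper limit on fitness. A ceiling on one end of the dependent variable tilts a linear model.

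The same value is used in three places: as target of the primary model, as yardstick in its validation, and as reference for two consumer estimates. An error in it therefore affects all three and is not exposed by any of them.

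**Working it through.** **1. The plan's own figure.** The overall F test with 6 predictors, f² = 0.15 and α = 0.05 (noncentral F with 6 and N − 7 degrees of freedom, λ = 0.15 N) gives power 0.898 at N = 122 and 0.901 at N = 123. The stated 123 is reproduced. Dividing by 0.85 gives 144.7, against the stated 144. Nothing in this point changes the sample size.

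**2. Effect of a ceiling on the slope.** Let *x* be the predictor score, scaled so that the true slope of VO2max (*y*) on *x* is 1. The test records min(*y*, *C*). Under joint normality, Cov(*x*, min(*y*, *C*)) = Cov(*x*, *y*) × P(*y* < *C*). The fitted slope is therefore 1 − *p*, where *p* is the share cut off.

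**3. Inputs.** Assumed, because the article gives none of them: mean 35, SD 8 mL/kg/min, R² = 0.60, ceiling *C* between 40 and 48. From the article: 144 participants.

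**4. Formulas.** With *z* = (*C* − 35)/8:

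- share cut off: *p* = 1 − Φ(*z*)
- mean loss over everyone: *m* = 8 × [φ(*z*) − *z p*]; mean loss among those cut off: *m/p*
- 1.5 SD of the predictor score: 1.5 × 8 × √0.60 = 9.30
- prediction error: −*m* − 9.30 *p* at +1.5 SD, and −*m* + 9.30 *p* at −1.5 SD

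**5. Results (mL/kg/min).**

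| Ceiling | *p* | of 144 | *m* | *m/p* | slope | error at +1.5 SD | error at −1.5 SD |
|---|---|---|---|---|---|---|---|
| 40 | 26.6% | 38 | 1.30 | 4.87 | 0.73 | −3.8 | +1.2 |
| 45 | 10.6% | 15 | 0.41 | 3.83 | 0.89 | −1.4 | +0.6 |
| 48 | 5.2% | 7 to 8 | 0.18 | 3.36 | 0.95 | −0.7 | +0.3 |

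For scale, the residual SD under the same assumptions is 8 × √0.40 = 5.1.

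**6. Robustness.** Simulation in SD units, with the share cut off set at 5%, 10%, 20%, 30% and 40%, gave slopes of 0.95, 0.90, 0.80, 0.70 and 0.60. The slopes were the same for R² of 0.5, 0.7 and 0.8 and, at R² 0.7, when the ceiling varied between persons (SD 0.5).

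**7. What validation would show.** At R² 0.7 with 20% cut off, mean absolute error is 0.395 SD against the recorded value but 0.465 SD against true VO2max. With no cut-off, both are 0.437 SD. The truncated reference makes the model look more accurate while it becomes less so.

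**8. Consumer estimates.** An accurate estimate, compared with a cut-off reference, appears too high by the missing amount: on average 3.4 to 4.9 mL/kg/min in the affected participants under the assumptions in step 3.

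**The case against.** **The size has no anchor in the document.** There is no VO2max distribution, no count of tests stopped for running and no speed for the later stages. With few such tests the bias is small; at a ceiling of 48 it is well inside the residual scatter. This stands, and it limits how serious the point can be said to be.

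**A walking-only reference may be deliberate.** The Discussion aims at hiking-specific capacity and the field test is a submaximal walk. This stands too. But the quantity is then peak VO2 during walking, and the article calls it something else. The label matters most in the Polar and Garmin comparison.

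**Details belong in a fuller document.** Criteria for accepting a test as maximal, and a form field for the stop reason, are commonly left out of an article. A reader might infer that their absence is the fault. The document does not support that, and the point does not need it: it rests on a stated stopping rule and a stated label that do not agree. The planned outlier screening and data cleaning would not settle it either, since submaximal tests are not named there.

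**The error is mostly conservative.** A reader might infer that the tool becomes unsafe. The larger error is under-prediction in fit hikers. Over-prediction in unfit hikers exists, because a capped outcome tilts both ends of the line, but it is 0.3 to 1.2 against a residual SD of 5.1.

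**Conclusion.** The inconsistency is real and touches the primary outcome. Followed as written, the plan uses lower bounds as exact values for anyone stopped for running before exhaustion. Mechanism and direction are well supported: a flatter slope, under-prediction of the fit, slight over-prediction of the unfit, and a validation step that cannot reveal it.

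The size is not established. Under the stated assumptions (mean 35, SD 8, R² 0.60, joint normality, fixed ceiling of 40 to 48), 5% to 27% of tests are affected and the slope is 5% to 27% too flat. Predictions are about 0.7 to 3.8 mL/kg/min too low at +1.5 SD and 0.3 to 1.2 too high at −1.5 SD. This is a range, not an estimate.

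A reader might go further and conclude that the primary model is invalid. The document does not support that, because it does not say how many tests ended at the start of running. The point should be fixed; it is not of the highest severity.

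**What to change.** Reconcile the sections in wording and analysis. No change to the stopping rule is proposed. Two routes are open.

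1. **Rename the reference.** Call it peak VO2 during walking throughout, and limit the conclusions of the model and of the device comparison to that quantity.
2. **Keep VO2max and handle the affected tests.** Identify tests stopped for running without maximal effort, using the stop reason from test records where available, gas exchange from the K5, peak heart rate and the terminal Borg value. Report their number. Treat these values as right-censored in the primary model (Tobit-type regression) and in the Polar and Garmin comparison.

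An analysis of maximal tests only may be added as a sensitivity analysis, with the caveat that it selectively removes the fittest and so selects on the outcome. At the upper end of the assumed range it would also leave 144 − 38 = 106 participants, below the 123 the plan requires.

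**Cost.** The first route costs wording only. The second gives somewhat wider intervals and assumes that the onset of running carries no further information on VO2max given the predictors. By the end of April 2022, 162 participants had been tested in the laboratory and 144 of them outdoors. The stop reason may therefore have to be recovered from records and data already collected.
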